### Study participants

The study participants are female breast cancer survivors (stage 0-IIIa), aged 18 years and older who were at least 12 months post-treatment and had a complaint of persistent, moderate to severe fatigue despite standard treatments. We detail eligibility criteria along with source of that material and the study personnel responsible for determining that criteria in Table
1. One of the principal investigators, who is a physician, reviews all eligibility documents and determines a woman’s suitability for participating in the study.

**Table 1 T1:** Eligibility Criteria vs. Source Document

**Criteria**	**Source**	**Assessor**
Female breast cancer survivors	Medical Records, Michigan Tumor Registry, Medical History & Physical Exam	Study Nurse, Study Coordinator
Cancer free	Medical Records, Michigan Tumor Registry, Medical History & Physical Exam	Study Nurse, Study Coordinator
Completed treatment (i.e., surgery, chemotherapy, radiotherapy, immunotherapy, etc.) at least one year prior	Medical Records, Medical History & Physical Exam	Study Nurse, Study Coordinator
Capable of self-administering acupressure	Observation at screening visit	Study Nurse, Study Coordinator
Complaint of fatigue	Brief Fatigue Inventory score of ≥ 4	Study Nurse, Study Coordinator
Pregnant or planning to become pregnant	Pregnancy test, Medical History & Physical Exam	Study Nurse, Study Coordinator
Fatigue causing comorbidities (e.g. anemia, fibromyalgia diagnosis prior to breast cancer)	Medical Records, Medical History & Physical Exam	Study Nurse, Study Coordinator
Medication changes	Review of Concomitant Medications, Medical History & Physical Exam	Study Nurse, Study Coordinator
Acupuncture/Acupressure w/in 6 months	Communication with potential participant	Study Coordinator
Non-Breast cancer diagnosis w/in 10 years	Medical History & Physical Exam	Study Nurse
Medications for insomnia	Medical Records, Review of Concomitant Medications	Study Nurse, Study Coordinator
Untreated major depressive disorder and suicidal ideations	PRIME-MD (‘several days’ indicated on question 2i)	Study Nurse, Study Coordinator
Final, overall eligibility	Potential participant’s final review of eligibility	Principal Investigator

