## Statistical issues

### Statistics and power analysis

Primary Aim: The primary aim of this study is to investigate the differential effects of different modes of acupressure on fatigue in breast cancer survivors. For this, we are focusing on three fatigue outcomes, namely, BFI, which will be administered weekly, a measure of average daily physical activity and a self-reported fatigue score, both based on Actiwatch-S data. A BFI is collected weekly and provides a measure of average degree of fatigue, a score that ranges between 0 and 10, with higher numbers indicating more fatigue. We will be analyzing the BFI outcome over phases. The first phase BFI is obtained by averaging week-1 to week-3 measures (mid-treatment). The second phase comprising of week-4 to week-6 measures indicates the status in the second half of the treatment phase (end-treatment). The final phase comprises of week-7 to week-10, the washout phase (washout). In order to investigate the change in BFI between the three study arms, we are using a mixed-effects regression analysis with average BFI in the three phases as the outcome, phase as the within-subjects factor, and group (RA, SA, standard of care) as the primary between-subjects factor. The baseline BFI level will be used as a covariate. We shall further adjust the model for key demographic variables such as age and ethnicity, as well as the baseline HADS score. A *subject* random-effect will be used to account for the clustering effect within the three measurements on the same subject. Of primary interest is the group*phase interaction, the significance of which will indicate differences in extent of decrease between the arms. Post-hoc analyses of phase difference within each arm will be carried out multiple comparison adjustment. Model diagnostics will be carried out to confirm the distributional assumptions and appropriate corrective actions (e.g. transformation) will be performed as needed.

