Two types of fatigue-related measures will be collected from the Actiwatch-S. The first is a daytime activity count per minute, which is calculated by dividing the total daily activity counts by the total daytime minutes. For each phase as defined above, we shall use the corresponding 21-day (or 28-day) average as appropriate. The second type of measure is obtained from the four self-reported readings of the VAS-F. The daily averages are obtained from the non-missing entries each day, and are then combined to provide the phase average the same way as the daytime activity count. The analytical framework is identical to that for BFI, albeit with the changed outcome.

A secondary analysis with BFI will also be carried out which investigates the difference in proportion of severely fatigued subjects (BFI ≥ 6) across the three study arms. The analytical framework will be that of a mixed-effects logistic regression model with severe BFI (yes/no) being the dichotomous outcome. Apart from group, phase, and group*phase interaction as primary covariates, the model will also be adjusted for baseline status of severity. Remaining covariates in the model are identical to those in the continuous BFI model. The clustering effect due to subject will be accounted for using a generalized estimating equations approach.

In order to assess the extent of association between the improvement in FACT-B and improvement in fatigue measure (specific aim #1 letter D), we shall create the change-scores (week 6 – baseline, week 10 – baseline) for FACT-B (both total and component scores), and BFI. Then we shall fit a linear mixed model similar to that for the original BFI analysis, with BFI change-score as outcome, and the FACT-B change-score as a time-varying covariate. There will not be any phase or week variable in the model. We shall restrict this analysis to the SA and RA arms only so that the group variable will consist of two levels. A group*FACT-B interaction in the model will investigate any differential association across the arms between the change-scores. The additional covariates and clustering adjustment would be similar to the BFI analysis.

Secondary Aims:

1. Assessing difference across study arms with respect to sleep parameters

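### The secondary severe-fatigue model appears to replace the continuous baseline BFI with a yes/no severity status: valid, but it gives up a little power at no saving

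*Protocol article*

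**What the plan says.** All of the modelling text is in the protocol article under Statistics and power analysis.

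- **Main BFI model.** The outcome is average BFI per phase. "The baseline BFI level will be used as a covariate". Further terms follow: "We shall further adjust the model for key demographic variables such as age and ethnicity, as well as the baseline HADS score".
- **Severe-fatigue model.** This secondary analysis compares the "difference in proportion of severely fatigued subjects (BFI ≥ 6") across the three arms, with group, phase and their interaction. On baseline, "the model will also be adjusted for baseline status of severity". The next sentence reads: "Remaining covariates in the model are identical to those in the continuous BFI model". On repeated measures: "The clustering effect due to subject will be accounted for using a generalized estimating equations approach".
- **Test of interest in the main model.** "Of primary interest is the group*phase interaction".
- **Entry.** Table 1 under Study participants requires a "Brief Fatigue Inventory score of ≥ 4", on a scale from 0 to 10.

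No power is stated for the severe-fatigue model.

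**The concern.** Between the two models the outcome changes from a score to yes/no, and the baseline term appears to change with it, from a level to a status. A binary outcome gives no reason to cut the baseline covariate as well; a logistic model takes a continuous baseline score without difficulty.

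The cut loses information because of where it falls. With entry from a BFI of 4, the lower category runs from about 4 to just under 6 and the upper from 6 to 10. The lower end is only approximate, because Table 2 schedules the BFI at screening and again at week 0. Within each category, women differ in their chance of a later phase average of 6 or more, and the yes/no term cannot use that difference. What is at stake is precision in comparing the arms on the proportion severely fatigued.

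**Working it through.** **1. How the two baseline terms relate.** The two descriptions run in parallel: baseline term first, then the other covariates. On that pattern, severity status stands where baseline BFI level stood, and the remaining covariates are age, ethnicity and HADS. This is the likelier reading. Read literally, however, the covariates of the continuous model include baseline BFI level, so the remaining covariates could include it too. The text does not settle the matter.

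**2. The nearest power figure in the plan.** Under Power analysis the article gives 0.82 for the interaction and more than 0.95 for the group effect in the continuous BFI model, at 100 per arm and 5%. Its inputs are mid-treatment means of 4, 3, 3 and end-treatment means of 4, 3, 2 (standard care, SA, RA), variances of 4 and 4, and ICC 0.5. Using a noncentral F:

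- Interaction: the changes are 0, 0, −1 and their squared deviations sum to 2/3. λ = n × (2/3) / (2 × 4) = 100 × 0.667 / 8 = 8.33, so power is 0.732. At 125 per arm (the target of 375 divided by 3), λ = 10.42 and power is 0.829.
- Group: the arm means over the two phases are 4, 3, 2.5 and their squared deviations sum to 1.167. λ = 100 × 1.167 / (4 + 4/2) = 19.4, so power is 0.982.

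The group statement is reproduced. The 0.82 is not reproduced at 100 per arm but is close to the value at 125; with the article's 100 simulations its standard error is about √(0.82 × 0.18 / 100) = 0.04. This is a separate matter and does not bear on the baseline covariate.

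**3. Simulation of the severe-fatigue model.** There were 1,500 simulated trials per setting, each analysed by a logistic GEE (independence working correlation, robust Wald tests) with group, phase and group-by-phase, under four baseline adjustments.

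Assumptions not in the article: baseline BFI normal with mean 5.5, truncated to 4–10 (51–58% severe at baseline); no dropout; the two treatment phases only; age, ethnicity and HADS omitted. Variances of 4/4 and 2/2 (subject/residual) were both run, since both give ICC 0.5.

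Power of the joint (2-df) group test at end-treatment:

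| Setting | No baseline | Yes/no | Continuous | Both | Yes/no to continuous |
|---|---|---|---|---|---|
| A. Protocol means, variance 4/4, 100 per arm | 0.826 | 0.840 | 0.851 | 0.851 | +1.1 points |
| B. Protocol means, variance 2/2, 100 per arm | 0.835 | 0.860 | 0.872 | 0.872 | +1.2 |
| C. Protocol means, variance 4/4, 125 per arm | 0.925 | 0.935 | 0.936 | 0.937 | +0.1 |
| D. Assumed higher means, variance 2/2 (ICC 0.5), 100 per arm | 0.714 | 0.734 | 0.753 | 0.753 | +1.9 |
| E. Assumed higher means, variance 3/1 (ICC 0.75), 100 per arm | 0.785 | 0.856 | 0.908 | 0.909 | +5.2 |

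D and E assume means of 5.5, 5, 5 at mid-treatment and 5.5, 4.9, 4.5 at end-treatment, so that 38–39% of standard care is severe at the end.

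Power of the group-by-phase test, yes/no to continuous: A 0.211 to 0.214; B 0.249 to 0.255; C 0.271 to 0.274; D 0.185 to 0.187; E 0.255 to 0.263. The largest change is 0.8 points.

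The simulation standard error of each power is about 0.01, so the smallest differences are not distinguishable from zero.

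**4. Simpler single-phase checks** (2-df group test, 100 per arm):

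- Protocol end-treatment means, baseline-outcome correlation 0.5: 0.918 to 0.931, or +1.3 points.
- Assumed SD 2 and severe rates of about 36%, 27% and 19%: 0.70 to 0.72 at correlation 0.5, 0.73 to 0.77 at 0.6, and 0.79 to 0.83 at 0.7, or +2 to +4 points.
- Other assumed smaller effects, correlations 0.5–0.7: from about 0.68–0.72 to about 0.72–0.79. The upper ends differ by 0.79 − 0.72 = 7 points before rounding is allowed for.

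Continuous adjustment gave the higher group-test power in every setting, and entering both terms did as well as the continuous score alone.

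**The case against.** The strongest reply is that the article never says the model adjusts for yes/no status alone. If the remaining covariates include baseline BFI level, both terms are in the model and nothing is lost: in setting A, both together give 0.851, the same as the continuous score. That stands. Replacement is an inference, though the likelier one, and the remedy has to cover both readings.

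Second, the loss is small on the protocol's own figures: about 1 point at 100 per arm, next to nothing at 125, and negligible for the interaction. The larger losses need means or correlations that the article does not give. This also stands.

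Third, the analysis is secondary, no power is claimed for it, the main model already uses the continuous baseline, and covariate coding in a secondary model may be settled in an analysis plan not shown here. This keeps the point minor. It does not remove it, because the article does name a baseline term here, and the less informative one.

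Two stronger inferences should be resisted. A reader might infer that the yes/no adjustment biases the comparison or leaves it confounded. It does not: adjusting a randomised comparison for a baseline category is valid, and incomplete use of baseline costs precision only. A reader might also carry the point over to the logistic model for PSQI above 7. The article states no baseline term for that model, so no such choice is shown there.

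**Conclusion.** The point holds as a minor one about efficiency and clarity. If severity status replaces the baseline score, the between-arm test of severe fatigue loses about 0 to 2 points of power at the protocol's means and ICC of 0.5. It loses about 2 to 8 points under assumed smaller effects or baseline-outcome correlations of 0.5 to 0.75. The individually tabulated settings in that second group give 2 to 5 points; the upper end comes from the rounded single-phase ranges and is the least certain. The group-by-phase test loses under 1 point throughout. If both terms are in the model, there is no loss and only the wording needs attention.

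These sizes rest on the assumed baseline distribution, no dropout and omission of the other covariates. The direction does not depend on one set-up: it was the same in the repeated-measures and the single-phase simulations.

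**What to change.** In the severe-fatigue paragraph of Statistics and power analysis, state that the model is adjusted for the continuous baseline BFI level, either in place of baseline severity status or beside it, and list the remaining covariates by name (age, ethnicity, baseline HADS). This settles the reading and aligns the two BFI models.

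The cost is one line of text. The score is already collected and already used in the main model, so no data, visits or participants are added. The change should be made before arm-level outcome data are examined.

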### Study aims and hypotheses

The hypothesis of this project is that self-administered RA will result in improvements in measures of PCRF, quality of life, and sleep quality, compared to SA and standard of care. To assess this hypothesis, our primary aim is to examine the effect of 6-weeks of RA compared to a regimen of SA or standard of care on fatigue as assessed by:

A. weekly self-report using the Brief Fatigue Inventory (BFI), our primary outcome.

B. objective daytime physical activity on a wrist worn accelerometer using average activity counts/minute.

C. fatigue severity assessed 4 times daily using a visual analog scale recorded on wrist-worn accelerometer.

D. quality of life as assessed by Long Term Quality of Life Instrument (LTQL).

Our secondary aims include investigating the effect of 6-weeks of RA compared to a regimen of SA or standard of care on sleep quality of BC survivors as assessed by:

A. monthly self-report using the Pittsburgh Sleep Quality Index (PSQI), our primary outcome.

B. daily sleep/wake diaries and nighttime actigraphy.

C. examining the relationships between improvements in sleep quality and improvements in quality of life for SA and RA, as assessed by LTQL.

Our other secondary aim is to assess activity parameters required for implementation of an acupressure treatment in a clinical setting including the time to onset of a clinically meaningful effect as well as the duration of effect following cessation of the intervention. These factors are currently unknown for acupressure.

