For sleep, we shall use the VAS-SQ measure to carry out our time to onset analysis. As in the case of fatigue, a 3-point drop from baseline in VAS-SQ for the first time will be considered as onset. Since the VAS-SQ measures are weekly, we shall employ a *discrete survival analysis* technique to analyze this data. A discrete survival model is a logistic regression model of the discrete-time hazards, and is easily implemented in most standard statistical softwares. As in the case for VAS-F, this analysis will be confined to subjects with a baseline VAS-SQ score of 3 or more.

We would analyze similarly the time to relapse since the end of treatment, which is defined as the first time a 3-point increase (VAS-F or VAS-SQ) from the six-week value, occurs. This part of the analysis will be restricted to subjects for whom an onset has occurred.

All statistical analyses will be carried out in SAS 9.3 and PASW version 19.

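### The analysis labelled aim 1D relates BFI change to FACT-B change in two arms, so the stated three-arm comparison of quality of life by LTQL has no analysis

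*Protocol article*

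**What the plan says.** The section Study aims and hypotheses sets the primary aim as "the effect of 6-weeks of RA compared to a regimen of SA or standard of care on fatigue as assessed by" four lettered items. The last reads "D. quality of life as assessed by Long Term Quality of Life Instrument (LTQL" (the instrument's abbreviation). The comparison in the stem is therefore RA against SA or standard of care, and item D attaches quality of life to it. The hypothesis at the head of that section also names quality of life among the outcomes expected to improve under RA compared with both other arms. Table 2 schedules LTQL at baseline, week 6 and week 10, and the list of subjective measures describes it.

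Statistics and power analysis refers to item D once: "In order to assess the extent of association between the improvement in FACT-B and improvement in fatigue measure (specific aim #1 letter D". It forms change scores from baseline to weeks 6 and 10 and fits a linear mixed model "with BFI change-score as outcome, and the FACT-B change-score as a time-varying covariate". It then says "We shall restrict this analysis to the SA and RA arms only so that the group variable will consist of two levels".

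Later in the same section, for onset of the sleep effect, the plan says "we shall use the VAS-SQ measure to carry out our time to onset analysis" and treats that measure as weekly.

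**The concern.** The aim and the analysis labelled with its letter differ in three ways: the instrument, the quantity estimated, and the arms included. Silence in a condensed article could be left to a statistical analysis plan. Here the article assigns a specific model to the aim, and that model does not answer it. A later plan that follows the aims section departs from the statistics section, and the reverse also holds.

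At stake is one of the four lettered items under the primary aim. Followed as written, the trial would collect LTQL three times per woman and have no planned comparison of it between arms. The model and comparators for quality of life would then still have to be settled, possibly with data in hand.

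**Working it through.** No figure in the plan needs reproducing. The check traces each instrument through the document and then asks what the stated model estimates.

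**Where each instrument appears**

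| Instrument | Aims | Table 2 | Measures list | Statistical section |
|---|---|---|---|---|
| LTQL | Aim 1D; also secondary sleep aim C | Baseline, weeks 6 and 10 | Yes | Not named |
| FACT-B | No | No | No | Aim 1D analysis only |
| VAS-SQ | No | No | No | Sleep onset and relapse only |

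FACT-B and VAS-SQ are also missing from the abbreviations list.

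**What the aim 1D model estimates**

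With Q for quality of life and i, t for woman and visit (week 6 or 10), the described model is

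ΔBFI(i,t) = b0 + b1·group(i) + b2·ΔQ(i,t) + b3·group(i)·ΔQ(i,t) + covariates + subject effect + error,

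with group taking two levels, RA and SA.

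- b2 is the association of quality-of-life change with BFI change in the reference arm.
- b3 is the difference in that association between RA and SA.
- b1 is the RA–SA difference in BFI change among women whose quality of life did not change.

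Aim 1D needs two other quantities: mean Q under RA minus mean Q under SA, and mean Q under RA minus mean Q under standard of care. In the model Q is a predictor, so no coefficient gives the first. The second cannot be obtained at all, because the standard-of-care arm is not in the data set. With 1:1:1 allocation of the target 375, each arm has 375 / 3 = 125 women. The model therefore uses about 250 and leaves out about 125, the arm that the aim names as a comparator.

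**Does reading FACT-B as LTQL solve it?**

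The change scores at weeks 6 and 10 fit the LTQL visits exactly, so a leftover instrument name is plausible. Making the substitution changes Q in the formula and nothing else: BFI stays the outcome and standard of care stays out.

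**Does another sentence cover LTQL?**

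The three-arm mixed model is stated for three fatigue outcomes: BFI, Actiwatch activity, and self-reported fatigue. The PSQI paragraph carries the same framework over to sleep. Its closing sentence, extending the methods to further outcomes, follows total sleep time and sleep efficiency and refers to those. None of these reaches LTQL.

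**VAS-SQ**

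The onset rule needs a 3-point drop and a baseline of at least 3, so scale and direction matter. The weekly phone calls name only the BFI as a questionnaire. The Pre-baseline section says the logbook holds questions on sleep quality, without giving their scale or timing. That is a possible source, and the document does not confirm it.

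**The case against.** The strongest reply concerns standing. BFI is named as the primary outcome, the power analysis for the primary aim rests on it, and the statistics section limits the primary aim to three fatigue outcomes. The abstract lists those same three and does not include quality of life among its secondary endpoints. Item D also sits oddly under a stem about fatigue. This stands: the mismatch does not touch the trial's main result, and it should be rated accordingly.

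A second reply is that the replacement instrument is obvious. LTQL is the only measure the document describes as a quality-of-life instrument, and item D names it. This also stands for the instrument, but it does not supply an outcome model or restore the third arm.

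A third is that the text openly calls its model an association, which is a legitimate question in itself. That is true; the fault lies in labelling it as the analysis of aim 1D.

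A reader might also infer more than the documents support:

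- **That no FACT-B data will exist.** The article only fails to list the instrument, and it is a condensed account.
- **That VAS-SQ has the same gap as aim 1D.** It does not. The sleep-onset analysis is specified, its restriction to RA and SA agrees with its own heading, and three-arm sleep comparisons are covered by the PSQI model.
- **That the VAS-SQ analyses cannot be run.** The logbook may hold the item. A missing label proves little, since VAS-F is not listed under that name either, yet the measures list describes the fatigue score entered in the Actiwatch-S.

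**Conclusion.** The contradiction is real and is confined to aim 1D. The document defines a three-arm comparison of LTQL, then assigns to it a two-arm association between BFI change and change in an instrument it does not list. Correcting the instrument name alone leaves the aim unanswered. The extent is one of four lettered items under the primary aim, with about 125 of 375 women (the standard-of-care arm at target enrolment) outside the analysis.

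This should be fixed, but it is not critical: the BFI analysis and its power basis are unaffected. The conclusion rests on the article alone. A fuller protocol or a statistical analysis plan may already contain an LTQL comparison, but the article's wording would still need to be reconciled with it. VAS-SQ is a minor listing query.

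**What to change.** 1. Replace FACT-B by LTQL in the statistics section.
2. For aim 1D, make LTQL at weeks 6 and 10 the outcome, in all three arms, using the protocol's existing mixed model as carried over to PSQI: group, week, group-by-week interaction, baseline LTQL, the stated covariates and a subject effect. With 3 arms and 2 post-baseline visits there are 3 × 2 = 6 cell means and 1 + 2 + 1 + 2 = 6 mean parameters apart from covariates, so treating week as continuous imposes no restriction on the arm-by-visit means. Report RA versus SA and RA versus standard of care. The aim speaks of 6 weeks of treatment, so the week-6 contrasts match it most directly. Which visit carries the test is for the trial team to fix in advance.
3. Keep the two-arm model of BFI change on LTQL change as a separate association analysis, without the aim 1D label.
4. State where VAS-SQ comes from (for example, a logbook item), its scale, direction and frequency, and add it to Table 2 and the measures list.

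The cost is a few sentences of analysis text and, for VAS-SQ, one table row and one measure description. LTQL is already scheduled at the three visits needed, so aim 1D requires no new data collection.

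### In the fatigue and quality-of-life association model, each arm's slope mixes differences between women with movement after acupressure stops, and the plan neither justifies nor tests that the two are equal

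*Protocol article*

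**What the plan says.** The model is set out under Statistics and power analysis in the Protocol article. Its purpose is "to assess the extent of association between the improvement in FACT-B and improvement in fatigue measure".

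- **Data:** "we shall create the change-scores (week 6 – baseline, week 10 – baseline) for FACT-B" and likewise for the BFI, so each woman contributes two rows that share one baseline.
- **Model:** a linear mixed model "with BFI change-score as outcome, and the FACT-B change-score as a time-varying covariate".
- **Time:** "There will not be any phase or week variable in the model".
- **Arms:** "We shall restrict this analysis to the SA and RA arms only". Differences between them are tested thus: "A group*FACT-B interaction in the model will investigate any differential association across the arms between the change-scores".
- **Clustering:** "The additional covariates and clustering adjustment would be similar to the BFI analysis". In that BFI analysis a subject "random-effect will be used to account for the clustering effect within the three measurements on the same subject".

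The section on Visit 4 (week 6) says that acupressure ends at that visit and is withheld for the following four weeks. Nothing in the text separates association between women from association within a woman over time.

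**The concern.** Both change-scores subtract the same baseline, so baseline cancels when a woman's two rows are compared. What is left within a woman is week 10 minus week 6, a period entirely after acupressure has stopped. The contrast between women is a different one: who improved more, on average over the two visits.

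A random-intercept model with one undivided covariate treats these two associations as equal. The protocol gives no ground for that. It treats weeks 7 to 10 as a separate washout phase, and its power section assumes that mean BFI rises by 1 point from end of treatment to washout in both acupressure arms (3 to 4 and 2 to 3).

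Two results are at stake. The reported extent of association could differ from the link between one woman's improvement and another's. The group interaction could also signal a different fatigue and quality-of-life link in the two arms when only the persistence of the quality-of-life change differs.

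**Working it through.** The protocol gives no figure for this model, so there is none to reproduce.

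**Inputs.** From the protocol: two change-scores per woman, a subject random effect, one slope per arm, and 100 women per arm (power section). Assumed, because the protocol gives no value for this model: *rx*, the correlation between a woman's two quality-of-life changes; *re*, the correlation between her two BFI residuals; and the true slopes *bB* (between women) and *bW* (within a woman, week 6 to 10). The power section's intra-class correlation of 0.5 is for BFI levels, not change-scores.

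**Step 1: the weights.** Split each woman's two rows into their mean and their difference. In units of the covariate and residual variances, the covariate variances are proportional to 1+rx (mean) and 1−rx (difference), and the residual variances to 1+re and 1−re. Generalised least squares then gives

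weight on bW = [(1−rx)/(1−re)] / [(1−rx)/(1−re) + (1+rx)/(1+re)]

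- rx = 0.5, re = 0.8: (0.5/0.2) / (0.5/0.2 + 1.5/1.8) = 2.5/3.33 = 0.75
- rx = 0.8, re = 0.5: (0.2/0.5) / (0.2/0.5 + 1.8/1.5) = 0.4/1.6 = 0.25
- rx = re: 1/(1+1) = 0.50

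Over 0.5 to 0.8 for both correlations the weight runs from 25% to 75%.

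**Step 2: the slope.** With rx = re = 0.7, bB = −0.6 and bW = −0.1, the model targets 0.5 × (−0.6) + 0.5 × (−0.1) = −0.35. Simulation with a week term added returned −0.35. With bB = bW = −0.6 it returned −0.60, so equal slopes give no distortion.

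**Step 3: the interaction.** Give both arms the same bB and bW, but let rx differ between arms. Take re = 0.7, 100 per arm, and slopes in residual SDs per SD of quality-of-life change. For rx = 0.8 against 0.4:

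- The weights on bW are 0.667/1.725 = 0.386 and 2.0/2.824 = 0.708.
- With bB = −0.6 and bW = −0.1, the arm slopes are −0.6 + 0.5 × 0.386 = −0.407 and −0.6 + 0.5 × 0.708 = −0.246, a difference of 0.161.
- The standard error is √(1/172.5 + 1/282.4) = 0.097, so z = 1.67 and the rejection probability is P(Z > 1.96 − 1.67), about 38%. Simulation gave 36% to 37%.

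| bB / bW | rx in the two arms | Arm slopes | Rejection by formula | By simulation |
|---|---|---|---|---|
| −0.6 / −0.1 | 0.8, 0.4 | −0.41, −0.25 | 38% | 36–37% |
| −0.6 / −0.1 | 0.8, 0.6 | −0.41, −0.31 | 17% | 14–17% |
| −0.6 / −0.1 | 0.7, 0.6 | −0.35, −0.31 | 7% | 7–9% |
| −0.6 / −0.4 | 0.8, 0.4 | −0.52, −0.46 | 10% | 11–12% |
| −0.6 / −0.4 | 0.7, 0.6 | −0.50, −0.48 | 5% | 6% |
| −0.6 / −0.6 | 0.8, 0.4 | −0.60, −0.60 | 5% | 5% |

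(The lower end of the simulated range in the second row is for re = 0.5.)

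**Step 4: the split.** In the first scenario of the table, a model with the woman-mean and the deviation, each with its own group interaction, returned −0.60 and −0.10. Each interaction rejected in about 5% of runs.

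**Step 5: the week term.** Adding a week term does not remove the mixing; the simulations in steps 2 to 4 all include one. Leaving it out adds a second problem. With the protocol's 1-point BFI rise after week 6, no individual-level association, and an assumed mean fall in quality of life of 0.2 to 0.8 SD, the slope was significant in 10% to 62% of runs. With the week term, rejection was 6% to 8%.

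**The case against.** A reader might infer that the slope answers neither question. The documents do not support that. If the between-woman and within-woman associations are equal, the slope answers both, and nothing in the protocol shows that they differ. The stated purpose does not say between women either; it defines improvement at both visits, and a pooled change-on-change slope is a legitimate summary. Nor is there literally one slope, since the interaction gives one per arm, each of them mixed.

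A reader might also take the 37% as the expected error rate. It needs two strong assumptions together: a sixfold gap between the slopes and a doubling of the correlation between two arms that follow the same once-daily schedule. With smaller gaps the excess mostly disappears.

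The remedy has limits too. If a woman's underlying improvement, rather than her observed mean, drives the association, the woman-mean slope is still mixed. With rx = 0.7 and slopes −0.6 and −0.1 it becomes (0.70 × −0.6 + 0.15 × −0.1)/0.85 = −0.51. It also averages in the week 10 change.

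Finally, the model needs respecifying anyway. FACT-B is in neither the study measures nor the visit table, and aim 1D names the Long Term Quality of Life Instrument (LTQL).

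All of this stands and limits the claim. What remains is that the article fixes this covariate in detail, and the equality on which its interpretation rests is neither argued nor tested.

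**Conclusion.** The concern holds in a limited form. As specified, each arm's slope is a weighted average of the between-woman association and the week 6 to 10 co-movement. It can be read as the stated association only if the two are equal. If they differ, the post-treatment part carries 25% to 75% of the weight for assumed correlations of 0.5 to 0.8. The interaction's false-positive rate then ranges from about 6% to about 37% across the assumed scenarios. None of these correlations or slopes comes from the protocol, so the figures show what is possible and do not estimate the bias in this trial.

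A reader might infer that the efficacy result is at risk. It is not: this supporting analysis has no power claim or decision rule attached, and the primary BFI comparison across arms is a separate model.

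**What to change.** Revise the aim 1D model text as follows:

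1. Use the quality-of-life instrument actually collected. The visit table has the LTQL at baseline, week 6 and week 10, so both change-scores can be formed.
2. Add a week term.
3. Replace the one covariate by two: each woman's mean of her two change-scores, and the deviation of each change-score from that mean. Give each its own group interaction.
4. Report the woman-mean slope as the association averaged over weeks 6 and 10, and the deviation slope separately as co-movement after treatment stops.

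If the association at the end of treatment is what is wanted, a model of the week 6 change alone is an alternative, because the woman-mean slope still includes week 10.

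The cost is one derived covariate, one extra interaction and a week term in the text, with slightly wider intervals on each slope. No new data are needed.
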